## Abstract

**Background:**

The quality of communication in oncology significantly impacts patients' health outcomes, as poor communication increases the risk of unnecessary treatment, inadequate pain relief, higher anxiety levels, and acute hospitalizations. Additionally, ineffective communication skills training (CST) is associated with stress, low job satisfaction, and burnout among doctors working in oncology. While acknowledging the importance of effective communication, the specific features of successful CST remain uncertain. Role-play and recorded consultations with direct feedback appear promising for CST but may be time-consuming and face challenges in transferring acquired skills to clinical contexts. Our aim is to bridge this gap by proposing a novel approach: On-site Supportive Communication Training (On-site SCT). The concept integrates knowledge from previous studies but represents the first randomized controlled trial employing actual doctor-patient interactions during CST.

**Methods:**

This randomized multicenter trial is conducted at three departments of oncology in Denmark. Doctors are randomized 1:1 to the intervention and control groups. The intervention group involves participation in three full days of On-site SCT facilitated by a trained psychologist. On-site SCT focuses on imparting communication techniques, establishing a reflective learning environment, and offering emotional support with a compassionate mindset. The primary endpoint is the change in percentage of items rated “excellent” by the patients in the validated 15-item questionnaire Communication Assessment Tool*.* The secondary endpoints are changes in doctors’ ratings of self-efficacy in health communication, burnout, and job satisfaction measured by validated questionnaires. Qualitative interviews will be conducted with the doctors after the intervention to evaluate its relevance, feasibility, and working mechanisms. Doctors have been actively recruited during summer/autumn 2023. Baseline questionnaires from patients have been collected. Recruitment of new patients for evaluation questionnaires is scheduled for Q1-Q2 2024.

**Discussion:**

This trial aims to quantify On-site SCT efficacy. If it significantly impacts patients/doctors, it can be a scalable CST concept for clinical practice. Additionally, qualitative interviews will reveal doctors' insight into the most comprehensible curriculum parts.

**Trial registration:**

April 2023 – ClinicalTrials.gov (NCT05842083). April 2023 – The Research Ethics Committee at the University of Southern Denmark (23/19397).

## Background

Communication between patients and doctors plays a central role in cancer treatment. Successful and effective communication not only strengthens the doctor‒patient relationship; it also enhances patients’ understanding of the treatment process [1], promotes shared decision making [2, 3], and improves patients’ quality of life [4]. Evidence suggests that individualized and empathic communication plays an important role in patient satisfaction, treatment adherence, empowerment, and in navigating the course of the disease [5].

In the field of oncology, communication is particularly complex due to the serious nature of the disease, the growing number of treatment options, and the often uncertain treatment outcomes with risk of recurrence [6]. To understand each patient’s feelings, ideas, concerns [7], and preferences [8] doctors must tailor their communication, which can be a challenging task [9].

Dissatisfaction with perceived communication is a frequent cause of patient complaints [10], and it likely occurs more frequently than officially reported [11]. Poor communication correlates with negative patient experiences and is associated with outcomes such as insufficient pain relief, reduced commitment to treatment decisions, higher risk of unnecessary treatments, increased anxiety levels, and more frequent acute hospitalizations [12, 13]. Analyzing the implications of inadequate communication in cancer care is highly complex, and the potential costs can be substantial, encompassing economic, social, and psychological burdens for both individuals and society [12].

Among doctors working in oncology, inadequate training in communication is correlated with distress, reduced job satisfaction, and emotional burnout [1, 14]. Clearly, this can lead to significant implications for the individual doctor, but overall, exhausted healthcare staff will provide poorer treatment and care [15, 16].

### Features of effective communication skills training

Evidence suggests that communication skills can be taught [17], but uncertainty remains as to the specific components contributing to successful communication skills training (CST) [6]. This is due to the diverse CST intensity, formats, and contents of existing studies along with the wide range of outcome measures used, which makes it difficult to conclude on the results.

When Bos-van den Hoek et al. [18] in 2019 synthesized findings from reviews of the past decade, including a Cochrane review from 2018 [6], certain elements emerged as potentially important factors in the design of CST interventions. Programs spanning over three days (24 h) appeared more effective than shorter programs [17], and post-training follow-up showed potential significance [19]. Training involving active skills practice with feedback on observed situations with real or simulated patients seemed more efficient [20, 21].

Role play with peers or actors combined with recorded consultations has been used in CST, but no trials used real patients during on‐site training [6]. Studies on CST with recorded consultations/role-play have shown a positive effect on key communication skills [22] and increased self-efficacy [23]. Two studies have demonstrated long-term maintenance of acquired skills [24, 25]. Until now, no effect on burnout has been demonstrated [26, 27].

### Psychologists may play an important role in a learner-centered CST approach

As described, communication skills training can hold many different formats. In the Cochrane review, most trials specified the use of “learner‐centered, experiential, adult education methods” conducted by experienced facilitators [6]. Training facilitated by a psychologist allows for involvement of critical elements in relationships and establishment of alliances with the patients [28]. In addition, a psychosocial foundation can facilitate a learner-centered setting prioritizing the needs and agendas of the trainees [29]. This creates a safe environment for educational and contemplative progression to take place.

### Research gap and study objectives

Until now, studies in CST have relied on role-playing, recorded conversations, group discussions or didactic teaching [6]. These approaches are time-consuming for the doctor, and the transfer of communication skills learned in a training environment may be challenging [30, 31].

To bridge this gap, we have developed a supportive communication training invention taking place in the daily clinic (On-site SCT) based on the current knowledge of effective CST. In the present study, trained psychologists facilitate the training in the outpatient clinic, thereby merging medical expertise with psychological insights. This innovative approach offers several potential advantages in terms of feasibility and efficiency. On-site SCT has the potential to facilitate direct skill transfer, provide personalized training, and promote interdisciplinary collaboration to address both physical and mental health aspects—all while the doctor remains in service.

## Hypotheses

Patients’ ratings of doctors’ performance in the area of interpersonal and communication skills will increase when doctors participate in On-site SCT.Participation in On-site SCT will increase the doctors’ self-evaluation in relation to communication efficacy and job satisfaction, and decrease their experience of burnout.

## Methods

### Setting

This study is a randomized, controlled, multicenter study with three participating sites: Vejle Hospital, Aalborg University Hospital, and Zealand University Hospital. Hypotheses are tested by comparing questionnaires before and after the intervention.

Each site has a study coordinator to ensure adherence to the intervention protocol. The project employs seven experienced psychologists (one person-year in total).

## Participants

### Patients

Patients attending a doctor's appointment at the outpatient clinic during the data collection periods are eligible to participate in the study. They will be encouraged to complete the Communication Assessment Tool (CAT) [32], a validated questionnaire, providing their evaluation of the doctor’s performance in the areas of interpersonal and communication skills. Each questionnaire is marked with the initials of the specific doctor, allowing for comparison between doctors in the intervention and control groups. When possible, questionnaires are distributed by study nurses or secretaries instead of the doctors themselves to reduce the risk of selection bias (i.e., the situation where doctors select the patients they hand a questionnaire). Questionnaires will be administered at baseline and evaluation. In case some patients do not wish to participate, their empty questionnaires will be collected to track the response rate.

Our aim was to collect questionnaires from all patients interacting with a doctor eligible for enrolment, as this approach will enable us to compare participating and nonparticipating doctors. Baseline questionnaires have been collected at all three sites during summer/fall 2023. The recruitment of new patients for evaluation questionnaires is scheduled for Q1-Q2 2024.

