## Sample size calculation

Approximately 80 out of the around 90 eligible doctors (89%) are expected to participate in the study.

To achieve a power of 80%, a sample size of 2,080 patients (1,040 in each group) will be obtained by sampling 40 clusters (doctors) with 26 patient questionnaires in each group. In total we thus aim to collect 4160 questionnaires. The proportion in the intervention group is assumed to be 0.28 under the null hypothesis and 0.34 [33] under the alternative hypothesis assuming a difference between the group proportions of 0.06. Due to the lack of international consensus in this research area, an absolute change of 6% was agreed upon by mutual consensus in the steering group, as we believe such change would represent a clinical relevant difference for the patients. The proportion in the control group is assumed to be 0.28. The sample size calculation is based on a two-sided Z Test (unpooled) with intracluster correlation (ICC) set at 0.005, and significance level of the test at 0.05.

Each cluster size of 26 completed questionnaires per doctor at baseline and evaluations aligns with the recommendations from the CAT developers [32]. To meet the target we aim to distribute 30–40 questionnaires per doctor. Staff at each outpatient clinic will assist in the process.

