### Limitations

The nature of the On-site SCT intervention does not allows for blinding of the participants or researchers to the group assignment. This may introduce bias and affect the interpretation of the results.

The study relies on voluntary participation of oncologists, which may introduce selection bias. The doctors who choose to participate may have a greater interest or motivation for improving their communication skills, which could affect the generalizability of the findings.

The CAT questionnaire is the only tool used to assess patients' perceptions in this study. It lacks cancer-specific validation in this particular setting, which could be considered a limitation [55]. While the CAT has been tested in various inpatient settings with no evidence of a ceiling effect [33, 56, 57], higher scores and a potential risk of a ceiling effect were observed when tested in family medicine and outpatient settings [32, 58]. If a ceiling effect is observed, we will apply appropriate statistical methods (Tobit models) to account for the data structure.

Long-term evaluation of the intervention is not within the scope of the study.

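### Unblinded doctors may sometimes choose which new patients rate them at evaluation, and the tracked response rate cannot show it because it counts only patients who were offered a form.

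*Protocol article*

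**What the plan says.** The section on patients sets the distribution rule for the questionnaire rounds: "When possible, questionnaires are distributed by study nurses or secretaries instead of the doctors themselves to reduce the risk of selection bias". It names the risk it has in mind as "the situation where doctors select the patients they hand a questionnaire". On monitoring, it says: "In case some patients do not wish to participate, their empty questionnaires will be collected to track the response rate". The raters at evaluation are a fresh sample: "The recruitment of new patients for evaluation questionnaires is scheduled for Q1-Q2 2024".

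The sample size section plans 26 completed forms per doctor at each round and adds: "To meet the target we aim to distribute 30–40 questionnaires per doctor". It also says that outpatient clinic staff will help. The limitations section states that the intervention "does not allows for blinding of the participants or researchers to the group assignment", and accepts that this may introduce bias, without linking it to who hands out the forms.

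The primary endpoint section expects patients in the two arms to be exchangeable because of the randomization and the large number of observations. It adjusts for site only and checks exchangeability by standardized differences, with values above 0.1 taken as imbalance. The patient data listed are sociodemographics, years with cancer, disease stage, whether this was a first meeting with the doctor, and whether relatives took part.

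**The concern.** Doctors are randomized; the patients who rate them at evaluation are not. They enter the sample after allocation, and in some clinics the person deciding who gets a form may be the doctor being rated, who knows the arm. Randomizing doctors gives no assurance that patients picked later are comparable. A large sample reduces random error and leaves selection bias untouched. Clustered robust variance widens the interval where needed but does not move the estimate.

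The monitoring tool does not cover this gap. Collecting empty forms tells the trial how many patients were offered a form and declined. It says nothing about patients who were passed over. A high and equal response rate in both arms is therefore compatible with selective offering in one of them. What is at stake is the between-arm contrast in the only primary endpoint.

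**Working it through.** **1. What each safeguard can see.**

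| Selection at evaluation | Response rate (forms offered) | Standardized differences |
|---|---|---|
| Patient offered, declines | Yes | No form data |
| Patient not offered, differs on a recorded characteristic | No | Possibly, as imbalance among returned forms |
| Patient not offered because of how the consultation went | No | No, unless related to a recorded characteristic |

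The planned numbers show the same thing. Obtaining 26 completed forms from 30 to 40 distributed implies a return of 26/40 = 65% to 26/30 = 87%. That figure is identical whether the 30 to 40 patients were consecutive or picked.

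**2. The plan's sample size.** Inputs from the sample size section: proportions 0.28 and 0.34, two-sided 5%, 80% power, ICC 0.005, 26 forms from each of 40 doctors per group, unpooled Z test.

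- Per group without clustering: (1.960 + 0.842)² × (0.28×0.72 + 0.34×0.66) / 0.06² = 928.8
- Design effect: 1 + 25 × 0.005 = 1.125
- Per group: 928.8 × 1.125 = 1,045, against 1,040 stated; power at 1,040 is 79.8%.

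The stated size reproduces.

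**3. Standard error with no true effect.** Effective size per group is 1,040 / 1.125 = 924.4. SE = √(2 × 0.28 × 0.72 / 924.4) = 0.0209, or about 2.1 points.

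**4. Illustrative shift (assumed inputs).** The article gives neither the share of forms that doctors hand out nor the share of patients passed over. Suppose a share u of an arm's patients is never offered a form and would have rated *excellent* at 10%, while the arm's true rate is 28%. The observed rate is (0.28 − 0.10u) / (1 − u).

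- u = 5%: 0.275 / 0.95 = 0.2895, a shift of 0.95 points
- u = 10%: 0.270 / 0.90 = 0.300, a shift of 2.0 points

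Only the difference between arms matters:

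| Passed over, one arm | Passed over, other arm | Net shift |
|---|---|---|
| 10% | 10% | 0 |
| 10% | 5% | 2.0 − 0.95 = about 1 point |
| 10% | 0% | 2.0 points |

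**5. Effect on the test.** For a net shift b, the two-sided false-positive rate is 1 − Φ(1.96 − b/SE) + Φ(−1.96 − b/SE).

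- b = 0: 5%
- b = 1 point: b/SE = 0.479, giving 7.7%
- b = 2 points: b/SE = 0.958, giving 16%

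Two points is one third of the 6-point target. A shift of the same size against the intervention would instead hide part of a true effect.

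**The case against.** Much can be said for the plan. Staff distribution is the default and was chosen to prevent this very bias; clinic staff are to assist; and exchangeability is checked on recorded characteristics. The risk is disclosed, so what remains is an incomplete safeguard and not an overlooked problem. All of that stands.

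Four stronger readings are tempting, and the documents do not support them.

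- *The bias favours the intervention.* A reader might infer that trained doctors have more reason to leave out a consultation that went badly. Nothing in the article says so. Forms in both arms carry the doctor's initials, so control doctors may care just as much. The article also does not say whether forms are handed out before or after the consultation, and selection on how it went needs the latter.
- *Counting empty forms is the only control.* It is not, for the reasons above.
- *Nothing will record who handed out a form.* This is a condensed article that refers to predefined analysis plans and a data entry manual, neither of which is shown. Such a record may exist. What the article itself fixes is the conditional distribution rule and the offered-form count.
- *The aim of covering all patients contradicts the 30 to 40 forms per doctor.* The aim, "Our aim was to collect questionnaires from all patients interacting with a doctor eligible for enrolment", is justified by comparing participating with nonparticipating doctors, which is a baseline analysis. The 30 to 40 is a target for securing 26 completed forms. Neither statement gives doctors the choice of patients.

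Since the endpoint is described as a change, selection that a doctor practises identically at baseline and evaluation could also cancel. Nothing described in the article would show whether it did.

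**Conclusion.** The point holds as a gap in a partly adequate safeguard. Unblinded doctors may sometimes decide which new patients rate them, and neither the tracked response rate nor the standardized differences would reveal selection on how the consultation went. If that selection differs by arm, the primary endpoint is biased, and nothing in the described analysis corrects it.

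The illustration, a net shift of 0 to about 2 points with a false-positive rate of 5% to about 16%, rests on assumed shares of patients passed over and an assumed 10% *excellent* rate among them. It uses the plan's 28%, ICC and cluster sizes. The upper end assumes no selection at all in the other arm. It shows how sensitive the test is and is not an estimate of bias in this trial. Because the evaluation round still lies ahead in the article, an inexpensive change is worth making.

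**What to change.** For the evaluation round:

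1. Offer forms to consecutive patients on each doctor's clinic list until the target is reached, whoever hands them out.
2. Mark on each form whether staff or the doctor distributed it.
3. Report by arm the forms offered and the forms returned, each over booked appointments in the collection window, so that patients never approached enter the denominator.
4. Add a sensitivity analysis of the primary endpoint restricted to staff-distributed forms, labelled supportive.

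If the full protocol or data entry manual already provides for any of these, it is enough to say so. The cost is a small clerical load: one mark per form and a count from the booking list. The restricted analysis has less power than a design that starts at about 79.8%, and it uses a subset that randomization does not protect, so it cannot replace the primary analysis.

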### Doctors

The doctors in this clinical trial are either in specialty training or are board-certified specialists in clinical oncology. All doctors employed at the three participating sites working at least 4 days/month in the outpatient clinic undergo screening for eligibility. The cutoff ensures study relevance by including doctors with diverse roles, from doctors with frequent patient contact to doctors with fewer interactions, mirroring real-life hospital scenarios. All participating doctors must provide an informed consent. Doctors whose contract expire during the study period or who are otherwise not able to participate in the full study period, e.g. due to maternity leave, are not eligible. Doctors who are not willing to participate are classified as nonparticipating. All doctors in this group are asked if they are willing to accept baseline collection of CAT questionnaires. A study flowchart is shown *in *Fig. 1.

**Fig. 1 Fig1:**
[figure not shown]
Study flowchart*.* CAT: Communication Assessment Tool, SE-12: Self-efficacy in Health Communication; CBI: Copenhagen Burnout Inventory; MTU: Medarbejdertilfredshedsundersøgelse (employee satisfaction survey)

Doctors have been actively recruited during summer (Vejle Hospital) and autumn (Aalborg and Zealand University Hospitals) 2023.

### Withdrawal criteria

Doctors are free to withdraw from the trial at any time without providing a reason. All dropouts will be registered.

### Randomization

Doctors are randomly assigned to the intervention and control groups in a 1:1 ratio using Research Electronic Data Capture (REDCap) version 13.1.25 and a block size of 2/4. Stratification based on location is implemented to ensure an equal distribution of workload among the psychologists. Stratification will also allow for site comparison in the analysis. The intervention will last 3–4 months at each site, depending on the number of participating doctors.

## Sample size calculation

Approximately 80 out of the around 90 eligible doctors (89%) are expected to participate in the study.

To achieve a power of 80%, a sample size of 2,080 patients (1,040 in each group) will be obtained by sampling 40 clusters (doctors) with 26 patient questionnaires in each group. In total we thus aim to collect 4160 questionnaires. The proportion in the intervention group is assumed to be 0.28 under the null hypothesis and 0.34 [33] under the alternative hypothesis assuming a difference between the group proportions of 0.06. Due to the lack of international consensus in this research area, an absolute change of 6% was agreed upon by mutual consensus in the steering group, as we believe such change would represent a clinical relevant difference for the patients. The proportion in the control group is assumed to be 0.28. The sample size calculation is based on a two-sided Z Test (unpooled) with intracluster correlation (ICC) set at 0.005, and significance level of the test at 0.05.

Each cluster size of 26 completed questionnaires per doctor at baseline and evaluations aligns with the recommendations from the CAT developers [32]. To meet the target we aim to distribute 30–40 questionnaires per doctor. Staff at each outpatient clinic will assist in the process.

